# Acceptability and feasibility of a 12-week yoga vs. educational film program for the management of restless legs syndrome (RLS): study protocol for a randomized controlled trial

**DOI:** 10.1186/s13063-019-3217-7

**Published:** 2019-02-15

**Keywords:** Restless legs syndrome, Yoga, Mind-body therapy, Behavioral intervention, Feasibility, Acceptability, Sleep, Mood, Quality of life

## Abstract

**Background:**

Restless legs syndrome (RLS) is a common and burdensome sleep disorder associated with profound impairment of health, well-being, and quality of life. Unfortunately, the medications used for RLS management carry risk of serious side effects, including augmentation of symptoms. Yoga, an ancient mind-body discipline designed to promote physical, emotional, and mental well-being, may offer a viable, low-risk new treatment. The primary objectives of this pilot, parallel-arm, randomized controlled trial (RCT) are to assess the acceptability and feasibility of a 12-week yoga vs. educational film program for the management of RLS.

**Methods:**

Forty-four adults with confirmed moderate to severe RLS will be recruited and randomized to a 12-week yoga (*n* = 22) or standardized educational film program (*N* = 22). Yoga group participants will attend two 75-min *Iyengar* yoga classes per week for the first 4 weeks, then one 75-min class per week for the remaining 8 weeks, and will complete a 30-min homework routine on non-class days. Educational film group participants will attend one 75-min class per week for 12 weeks and complete a daily RLS treatment log; classes will include information on: RLS management, including sleep hygiene practices; other sleep disorders; and complementary therapies likely to be of interest to those participating in a yoga and sleep education study.

Yoga and treatment logs will be collected weekly. Feasibility outcomes will include recruitment, enrollment, and randomization rates, retention, adherence, and program satisfaction. Program evaluation and yoga-dosing questionnaires will be collected at week 12; data on exploratory outcomes (e.g., RLS symptom severity (IRLS), sleep quality (PSQI), mood (POMS, PSS), and health-related quality of life (SF-36)) will be gathered at baseline and week 12.

**Discussion:**

This study will lay the essential groundwork for a planned larger RCT to determine the efficacy of a yoga program for reducing symptoms and associated burden of RLS. If the findings of the current trial and the subsequent larger RCTs are positive, this study will also help support a new approach to clinical treatment of this challenging disorder, help foster improved understanding of RLS etiology, and ultimately contribute to reducing the individual, societal, and economic burden associated with this condition.

**Trial registration:**

ClinicalTrials.gov, ID: NCT03570515. Retrospectively registered on 1 February 2017.

**Electronic supplementary material:**

The online version of this article (10.1186/s13063-019-3217-7) contains supplementary material, which is available to authorized users.

## Background

Restless legs syndrome (RLS) is a distressing sleep and sensorimotor disorder characterized by a compelling urge to move the legs, which is usually accompanied by unpleasant sensations in the legs that begins or worsens during periods of inactivity, is worse at night, and is at least partially relieved by movement [1]. As detailed in our recent reviews [2, 3], RLS affects up to 29% of US and European adults, with estimated prevalence rates averaging 12% in the general population, and 19.5% in primary care patients [3]. Up to 65% or more of those affected suffer moderate to severe symptoms [3]. While increasingly recognized as a disorder of significant clinical and economic import [3–7], the etiology of RLS remains poorly understood [8–10]. Currently, the primary underlying causes of RLS are thought to be genetic predisposition, dopaminergic dysfunction, and deficiencies in iron metabolism [8–14], although these factors have to date offered only a partial explanation [2]. As discussed in our recent papers [2, 3, 15], emerging evidence suggests that autonomic and hypothalamic-pituitary-adrenal (HPA) axis dysregulation may also play an important role in RLS pathogenesis and progression.

RLS is associated with significant sleep disturbance [6, 16, 17], the most common presenting complaint of those seeking medical care for RLS [18, 19], and is a major cause of chronic sleep loss [20]. Recent studies suggest that up to 40% of those with insomnia suffer from RLS [21, 22]. Likewise, mood disturbance is common in those affected by RLS [16, 23], and can both result from, and contribute to, sleep deficits [24]. Recent community-based studies suggest that RLS may also be linked, in a bidirectional manner, to cardiovascular disease (CVD), stroke, and key components of the metabolic syndrome [2, 8, 9, 25], associations that may be in part mediated by RLS’s adverse effects on sleep and mood [26, 27]. RLS leads to significant impairment of daily functioning and quality of life, increased health-related costs, and declines in productivity that are comparable to those reported in other serious chronic disorders, including diabetes, hypertension, Parkinson’s disease, and stroke [6, 7, 26, 28, 29]. Collectively, these studies suggest that RLS is a serious, chronic condition of major public health import, affecting a large percentage of the adult population and exacting a significant toll in terms of health, quality of life and economic cost.

There is no cure for RLS, with current treatments aimed at symptom management. Pharmaceuticals, notably dopaminergic agents and anti-seizure medications (α2δ ligands) remain first-line treatments for RLS, with opioids and, less commonly, benzodiazepines, used as second-line therapies [25, 26, 30–32]. Unfortunately, all medications used for RLS management carry risk of serious side effects (with 6–80% of patients affected, depending on the medication and duration of treatment) [26, 31, 33]. Among the most troubling is augmentation of symptoms, a serious clinical problem which has been reported for all dopaminergic drugs and certain opioids, with risk increasing with longer treatment duration [25, 26, 30, 31, 34]. For example, in a recent community-based study of 266 RLS patients who had been treated with dopaminergic agents, only 25% had no evidence of augmentation [35]. Other common side effects include somnolence and general toxicity (all RLS medications); impulse control disorders (dopamine-receptor agonists); dyskinesias (dopaminergic agents), nausea and vomiting (dopaminergic agents, opioids); mood disturbances (α2δ ligands, opioids, benzodiazepines); weight gain (α2δ ligands); addiction (opioids, benzodiazepines); increased risk for falls (opioids, benzodiazepines), and other adverse sequelae [25, 26, 30, 31, 34, 36–44]. In addition, these effects can be particularly problematic in older adults [45, 46], who suffer disproportionately from RLS [42, 47]. In addition, the efficacy of all RLS medications commonly diminishes with time [31, 48–51], leaving patients with few treatment options. Given these drawbacks, investigation of safe, sustainable, nonpharmacologic therapies, that may not only alleviate RLS symptoms, but address associated comorbidities and apparent risk factors, is clearly warranted.

However, despite current clinical guidelines, including recent recommendations from the International RLS Study Group Task Force that medications be used only to treat “clinically significant symptoms that cannot be effectively managed behaviorally” [31], behavioral treatments remain largely untested and rarely implemented in practice. Specifically, although lifestyle changes and relaxation therapies, including yoga, are recommended for those suffering RLS [10], rigorous supporting research is lacking. To our knowledge, aside from our pilot studies [15, 52] only three small published trials have examined the potential benefits of lifestyle/behavioral interventions for individuals with RLS. These include a pre-post trial of cognitive behavioral therapy in 25 adults with primary RLS and psychosocial impairment, and two studies evaluating the effects of a 12–16-week exercise program vs. usual care on RLS symptoms: a non-randomized controlled trial in 14 hemodialysis patients [53] and a randomized controlled trial (RCT) of 23 community-dwelling older adults [54]. All reported significant improvement in RLS symptoms among participants assigned to the active intervention vs. the control group [53, 54] or baseline [55], suggesting that behavioral therapies may benefit those with RLS.

### Study rationale

Supported by our strong preliminary findings, drawing on the strengths of multiple disciplines, and testing a novel, clinical treatment paradigm, the proposed study will be the first RCT to rigorously assess the feasibility and acceptability of a promising mind-body therapy (yoga) for alleviating RLS symptoms and symptom burden. The study will provide essential preliminary data for a larger RCT to assess the efficacy of yoga for RLS management, and to evaluate the long-term effects of this novel therapy. Most important, this study will, in providing the foundation for the first rigorous trial of a novel behavioral therapy for RLS, have the potential to significantly alter the clinical management of this common and burdensome disorder.

As detailed above, medications used in RLS management carry risk of serious side effects that are especially problematic for older adults, and are often inappropriate for long-term use. Clearly, there is a need to investigate potentially safer, sustainable, low-cost therapies that are suitable for long-term use, and that have the potential not only to attenuate RLS symptoms, but to address the common comorbidities that may both result from, and contribute to, RLS. Particularly urgent is the investigation of promising patient-centered therapies that may enable and encourage patients to effectively manage their own health. While current guidelines indicate that behavioral management should comprise first-line treatment for RLS, and yoga and other relaxation therapies are sometimes recommended to RLS patients [56], rigorous supportive research is lacking. Findings from our two small, proof-of-concept studies suggest that yoga may significantly reduce RLS symptoms, improve sleep, and enhance mood, and decrease blood pressure in adults with RLS; observed effect sizes in these small trials were similar or superior to those reported in RLS drug trials [57–63], suggesting that yoga may offer a viable, multi-faceted, low-cost new treatment that is safer and more suitable for long-term use, and that has the potential to address symptoms as well as contributing factors.

An ancient mind-body discipline designed to promote physical, emotional, and mental well-being [64], yoga continues to gain popularity in the US, with over 13 million Americans reporting use of yoga in 2007 [65]. Our recent exploratory studies suggest that yoga may attenuate RLS symptoms, improve sleep, enhance mood, decrease stress, and reduce sympathetic activation in adults with RLS [15, 66], with observed effect sizes similar to, or greater than, those reported in trials of established drug treatments [57–63]. Numerous studies have shown yoga to improve quality of life, enhance well-being, and reduce pain, outcomes of clear relevance to RLS sufferers [67–75]. In addition, evidence from controlled trials by our group and others suggest that yoga may also improve indices of metabolic and autonomic function linked to both RLS and CVD risk [2, 9, 76–80]. Yoga has logistical advantages as well. Typically, a gentle practice with no appreciable side effects, yoga is relatively simple to learn and inexpensive to implement, and can be safely performed by a broad range of populations, including chronically ill, elderly, and even disabled adults [81–86]. The practice of yoga often brings immediate positive benefits, including feelings of relaxation and tranquility, helping to encourage continued adherence [77]. However, despite the promise of yoga as a safe, sustainable, cost-effective treatment for RLS, rigorous controlled studies are lacking.

### Design

This study will be a pilot, parallel-arm, community-based, RCT to assess the feasibility and acceptability of a 12-week yoga program vs. a 12-week educational film program for the management of RLS in adults aged ≥ 18 years with confirmed moderate to severe RLS. The protocol addresses the elements described in the Standard Protocol Items: Recommendations for Interventional Trials (SPIRIT) checklist (Additional file 1).

### Objectives

#### Primary objective

Our primary goal is to assess the acceptability and feasibility of a 12-week yoga vs. educational film program for RLS management in adults with moderate to severe RLS. Primary aims are as follows:Aim.1a. Assess participant recruitment and enrollment rates and determine optimal recruitment strategies. Reasons for refusal will be recorded and the information used to develop and implement strategies to address these barriers where appropriateAim.1b. Determine participant retention rates and adherence in the yoga and educational film groups, with 80% retention, 80% class attendance, 75% home practice (yoga group), and 80% completion of weekly logs serving as benchmarks for acceptability. Information on barriers to adherence will be collected and used to inform ongoing strategies to enhance compliance

#### Secondary objectives

Our secondary objectives include the assessment of treatment fidelity in the two programs, as well as participant willingness to enroll in yoga programs of varying duration and intensity. In addition, we will measure RLS symptom severity, sleep quality, mood, and health-related quality of life at baseline and 12 weeks to obtain effect size estimates for these exploratory outcomes. This information will provide critical data on which to base our planned larger RCT to determine the efficacy of yoga as a potential therapy for RLS. Secondary aims are as follows:Aim.2.1. Monitor and assess treatment fidelity in the yoga and educational film programs, using specific metrics to gauge fidelity. Lapses in fidelity will be recorded and the data used to inform strategies to address these lapsesAim.2.2. Assess the effect sizes at week 12 of a beginner yoga and a structured educational film program for RLS symptoms and related key exploratory outcomes (sleep quality, mood, perceived stress, and health-related quality of life) in adults with moderate to severe RLS, using well-validated, self-report instruments commonly employed in evaluating RLS treatments. Effect size estimates for these exploratory outcomes will provide critical data on which to base sample sizes in future larger trials, as well as provide important preliminary information on sensitivity of specific endpoints to change with a 12-week yoga interventionAim.2.3. Determine acceptable doses of yoga for a trial by assessing participant willingness to complete, as well as preference for yoga programs of the following duration and intensity: 8 weeks, 16 classes (2x/week); 12 weeks, 16 classes (2x/week for first 4 weeks, 1x/week thereafter); 16 weeks, 16 classes (1x/week). Acceptability and preferences will be evaluated using a self-report questionnaire administered to all participants at the follow-up assessment visit

## Methods

### Participants

Forty-four ambulatory, overall healthy adults aged ≥ 18 years with confirmed moderate to severe RLS will be recruited and randomized to a 12-week beginner yoga program (*n* = 22) or a standardized 12-week educational film program (*N* = 22), modeled on interventions used in our previous trials [15, 87] (see Fig. 1).

**Fig. 1 Fig1:**
[figure not shown]
Study flow diagram

#### Inclusion criteria

Study participants will be ambulatory adults ≥ 1 years of age with moderate-severe RLS, defined as:Symptoms that meet all five of the International RLS Study Group’s essential diagnostic criteria for RLS [1, 88] (i.e., (1) an urge to move the legs, often associated with discomfort or disagreeable sensations in the legs, that (2) begins or worsen during periods of rest or inactivity; (3) is partially or totally relieved by movement; (4) is worse or only occurs in the evening or night; and (5) is not solely accounted for by another condition (e.g., leg cramps, positional discomfort, habitual foot-tapping))RLS symptoms at least 1x/week for the previous 3 monthsA score of at least 2 points (moderate) IRLS question 6: “How severe was your RLS as a whole?” [89, 90]; andConfirmation of RLS diagnosis and study eligibility by a physician trained in sleep medicine; these criteria will help ensure exclusion of mimics (e.g., leg cramps, positional discomfort, arthritis pain, etc.) [20, 91]. Additional criteria include: willingness and ability to complete the 12-week yoga or educational film program and all study assessments; and willingness to avoid use of any new drugs or treatments other than the assigned intervention.

#### Exclusion criteria

Exclusion criteria are as follows: practiced yoga within the past year; currently on anti-psychotic medication; changed dosage of dopaminergic agents (e.g., levodopa, ropinirole, pramipexole) or any other central nervous system agents (e.g., sedative hypnotics, GABA analogs, narcotic analgesics, antiadrenergic agents, or anticonvulsants) within the past 3 months; hemoglobin (Hb) < 12 g/dL for women,< 13 g/dL for men; any orthopedic, neurologic, or other condition that might prevent safe completion of a 12-week yoga program or confound assessments (e.g., neuropathy; Parkinson’s disease; stroke; rheumatoid arthritis; renal failure; sleep apnea; recent (within the last 6 months) myocardial infarction; heart failure; cancer (other than non-melanoma skin cancer); pregnancy, or within 6 months post-partum). These medical exclusion criteria are consistent with those commonly employed in trials of RLS drugs and other RLS interventions [54, 92–96].

### Sample size

We performed a simulation study to determine the total sample size required to derive precise estimates of effect sizes for a two-arm randomized trial using a 1:1 randomization scheme for the primary intervention (yoga) and the educational film program; estimates were based on regression models using multiple simulations and scenarios, and specifically accounting for heterogeneity of effects. We considered seven combinations of effect sizes at 23 different sample sizes for total of 161 effect and sample size combinations. For each combination we ran 5000 simulations for a total of 805,500 simulations. The seven effect-size combinations were structured under the conservative assumption that all interventions would lead to a small to moderate improvement in outcomes and that the yoga intervention would lead to an improvement equal to or greater than the comparator condition. We used repeated simulations to determine the required post-attrition total sample size needed to obtain precise estimates of all three treatment effects under an intent-to-treat (ITT) analysis of variance (ANOVA) analysis. Based on findings of the simulation study and assuming 20% attrition, a sample size of 44 participants will permit reasonably precise estimates (within 95% confidence intervals of the true effect size value) for the two interventions, as well as reasonable estimates of recruitment, randomization, and adherence rates; moreover, estimates remain robust even at 30% attrition. Thus, the study will be adequately powered even if effect sizes for the yoga program are substantially smaller, and attrition rates greater than observed in our pilot studies [15, 66].

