*Treatment effect sizes* (*A.2.2*), based on between-group differences in change over time, will be estimated using one-way ANOVA models. Effect size estimates will be calculated using both ITT (primary) and per-protocol analyses. These unbiased estimates of intervention effect size will inform sample size determination for our planned future efficacy trial [147]. Scores on *the Yoga-dosing Questionnaire* (*A.2.3*) will also be assessed using descriptive statistics to determine optimal scheduling and maximum acceptable dosing of yoga for our future trial.

*Missing data*: every effort will be made to minimize missing data relevant to all aims. If missing data does occur and the missing-data pattern (probability model) is not missing completely at random (MCAR), then we will consider approaches appropriate for missing at random (MAR) and missing not at random (MNAR). If the pattern or structure of the plausible missing data suggests MAR, either the EM algorithm [148], inverse weighting [149], or multiple imputation (MI) [150, 151] will be used and the missing-data mechanism will be constructed from the collected data [150, 152, 153]. The selected method will reflect the appropriateness of the method to best estimate the underlying missing-data mechanism [148–150, 152]. Participant characteristics will be assessed, including demographic and lifestyle characteristics, RLS severity, medical history, health-related factors, and baseline questionnaire scores for the estimation of plausible models (i.e., MCAR, MAR, and MNAR) for the missing-data mechanism. While we will not be able to definitively test if the missing data are MNAR, If there are indicators suggestive of MNAR (e.g., drop-outs differ significantly from non-drop-outs in key characteristics), we will use MI in conjunction with a sensitivity analysis to provide a set of plausible conclusions recognizing that each conclusion will be predicated on the assumptions necessary for constructing a MNAR missing-data mechanism model [150, 153].

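### The statements that 44 participants give an adequately powered study and reasonably precise effect sizes do not follow for the small-to-moderate effects that the sample-size section simulates

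*Protocol article*

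**What the plan says.** All but the last of these statements are in the Sample size section of the protocol article.

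- The design is a "two-arm randomized trial using a 1:1 randomization scheme", with 22 participants per arm.
- The simulated scenarios assume a small to moderate improvement under every intervention, with yoga doing at least as well as the comparator. No numerical effect size, SD, significance level, target power or interval width is given.
- On precision: "assuming 20% attrition, a sample size of 44 participants will permit reasonably precise estimates (within 95% confidence intervals of the true effect size value", and "estimates remain robust even at 30% attrition".
- On power: "Thus, the study will be adequately powered even if effect sizes for the yoga program are substantially smaller". The rest of the sentence adds higher attrition and names the pilot studies as the comparator. Study rationale describes the pilot effects only as similar or superior to those in drug trials.
- On the simulation itself: seven effect combinations at 23 sample sizes, then "For each combination we ran 5000 simulations for a total of 805,500 simulations". The aim is described as obtaining "precise estimates of all three treatment effects".
- Statistical methods, under treatment effect sizes (A.2.2), estimates between-group differences in change by one-way ANOVA and adds: "These unbiased estimates of intervention effect size will inform sample size determination for our planned future efficacy trial".

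**The concern.** The section claims two properties for a sample of 44: adequate power and reasonable precision. Neither comes with a number that would let a reader check it. With about 35 people analysed, a two-group comparison has little power for anything short of a very large effect, and the interval around an effect estimate is wide. The precision criterion looks empty: a valid 95% interval covers the true value about 95% of the time at any sample size, so coverage alone cannot single out 44.

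What is at stake is how the results are read. The objectives and Statistical methods both pass these effect-size estimates on to the planning of an efficacy trial. If readers have been told that the estimates are precise and the study adequately powered, they may take a null difference as evidence of no effect, or a large one as a reliable planning value.

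**Working it through.** **Inputs from the article.** N = 44, 1:1; attrition 20% or 30%; analysis of the between-group difference in change by one-way ANOVA, which with two arms is the two-sample t-test.

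**Assumptions (not in the article).** Two-sided 5% level; effects in SD units; small to moderate read as d = 0.2 to 0.5 for the yoga-film difference. This last reading is generous. The text applies the phrase to each arm's own improvement, so if both arms improve by 0.2 to 0.5 and yoga is no worse, the difference is only 0 to 0.3.

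**The plan's own figures.** N = 44 cannot be reproduced, because no numerical criterion is given. Two parts can be checked:
- Attrition: 44 × 0.8 = 35.2, about 35 completers (18/17); 44 × 0.7 = 30.8, about 31 (16/15).
- Simulation count: 7 × 23 = 161, as stated; 161 × 5000 = 805,000, not 805,500.

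**Power.** Noncentral t with n1 + n2 − 2 degrees of freedom and noncentrality d × √(n1n2/(n1 + n2)). For 18/17 and d = 0.5 this is 0.5 × √(306/35) = 1.48, against a critical value of 2.03, which gives 30%.

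| Analysed | d = 0.2 | d = 0.3 | d = 0.5 | d giving 80% power |
|---|---|---|---|---|
| 44 (22/22) | 10% | 16% | 37% | 0.86 |
| 35 (18/17) | 9% | 14% | 30% | 0.98 |
| 31 (16/15) | 8% | 13% | 27% | 1.04 |

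More favourable settings do not rescue the claim. With 35 completers, a one-sided 5% test gives 14% to 42% over d = 0.2 to 0.5. Baseline adjustment with a correlation of 0.7 gives 13% to 52%, and at most 62% with no attrition. If the difference is 0.3 or less, power with 35 completers and the two-sided test is at most 14%.

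**Precision.** Half-width = 1.96 × √((n1 + n2)/(n1n2) + d²/(2(n1 + n2))).
- 35 completers, d = 0.5: 1.96 × √(0.1144 + 0.0036) = 1.96 × 0.343 = 0.67. Interval: 0.5 ± 0.67, or −0.17 to 1.17.
- 31 completers, d = 0.5: 1.96 × √(0.1292 + 0.0040) = 1.96 × 0.365 = 0.715. Interval: −0.22 to 1.22. Over d = 0.2 to 0.5 the half-width is 0.71 to 0.72.

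Such an interval cannot separate no effect from a very large one. A within-arm change would have a half-width of about 0.47 to 0.51 SD with 35 completers, which is also wide.

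**The precision criterion.** In a simulation of 95% intervals for a two-group difference, coverage was 95.0%, 94.9% and 95.1% at 5, 18 and 100 per arm, while the mean half-widths were 1.41, 0.67 and 0.28 SD. Coverage does not depend on sample size; width does. The article states coverage and omits width.

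**Feasibility rates, for comparison.** If 18 of 22 in one arm are retained (82%), the exact 95% interval is 60% to 95%.

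**The case against.** The strongest reply is that this is a feasibility and acceptability pilot. Its efficacy outcomes are exploratory, no efficacy test or success threshold is stated, and the declared aim is estimation. That stands: low efficacy power is not a fault in this design, and a reader should not infer that the trial is too small for its primary aims. What does not stand is the explicit statement that the study is adequately powered. If the word is taken loosely to mean precise, a half-width of about 0.67 SD does not support it either.

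Second, the words substantially smaller refer to the pilot effects. A reader might infer that the article claims adequate power for effects smaller than small to moderate; the full sentence does not say that. The pilot effects are not quantified, so how far the literal claim fails cannot be settled from the article. If the pilots had shown d well above 1, a reduced effect near 1.0 would have about 82% power with 35 completers. That lies outside the range the section says it simulated.

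Third, the article says reasonably precise and sets no width that it then misses, and numerical simulation criteria may sit in the full protocol. This is fair, and the criticism is limited to the criterion as worded.

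Fourth, a reader might infer that the efficacy trial will be sized on the observed d alone. Under that rule, with a true d of 0.5 and 35 completers, the later trial's real power would fall below 50% whenever the observed d exceeded 0.5 × 2.80/1.96 = 0.714. The chance of that is about 27%, and the chance of an observed d at or below zero is about 7%. But Statistical methods says only that the estimates will inform the sample size, and the objectives say that future sample sizes will be based on them. Neither states that rule, so these figures show a risk and do not describe the plan.

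Finally, the count error is trivial, and the three effects might be yoga, film and their difference. The text does not say.

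**Conclusion.** The power and precision statements in the Sample size section are unsupported for the section's own scenarios. Under a two-sided 5% test and a between-arm d of 0.2 to 0.5, both assumed, power is about 9% to 30% at 20% attrition and 8% to 27% at 30%. An effect of about 1 SD is needed for 80%. The expected half-width for d is roughly two thirds of an SD or more, and the stated criterion cannot justify 44. One-sided testing or baseline adjustment does not change the conclusion, and a difference below 0.3 would make it worse.

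Severity is moderate. The error is confined to what is claimed for the sample size. The primary aims, the retention and adherence benchmarks and the analyses are unaffected, and nothing here shows that more participants are needed.

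**What to change.** In Sample size:
- Delete the claim of adequate power.
- Replace the phrase about 95% confidence intervals of the true value with the expected half-widths for d: about 0.67 SD with 35 completers and 0.71 SD with 31, giving the assumptions.
- Add the precision of the feasibility rates, for example 18/22 = 82%, exact 95% interval 60% to 95%.
- Correct the simulation total to 805,000.
- Say which three treatment effects were simulated, or reconcile the phrase with the two-arm design.

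In Statistical methods, under treatment effect sizes: say that the observed effect size will be reported with its confidence interval, and that the later trial will not be sized on the point estimate alone.

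The cost is wording only, with no extra participants and no change to the analysis. The stated properties of the design become less favourable.
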